## Abstract

**Introduction:**

People who sustain a hip fracture are typically elderly, frail and require urgent surgery. Hip fracture and the urgent surgery is associated with acute blood loss, compounding patients’ pre-existing comorbidities including anaemia. Approximately 30% of patients require a donor blood transfusion in the perioperative period. Donor blood transfusions are associated with increased rates of infections, allergic reactions and longer lengths of stay. Furthermore, there is a substantial cost associated with the use of donor blood. Cell salvage and autotransfusion is a technique that recovers, washes and transfuses blood lost during surgery back to the patient. The objective of this study is to determine the clinical and cost effectiveness of intraoperative cell salvage, compared with standard care, in improving health related quality-of-life of patients undergoing hip fracture surgery.

**Methods and analysis:**

Multicentre, parallel group, two-arm, randomised controlled trial. Patients aged 60 years and older with a hip fracture treated with surgery are eligible. Participants will be randomly allocated on a 1:1 basis to either undergo cell salvage and autotransfusion or they will follow the standard care pathway. Otherwise, all care will be in accordance with the National Institute for Health and Care Excellence guidance. A minimum of 1128 patients will be recruited to obtain 90% power to detect a 0.075-point difference in the primary endpoint: EuroQol-5D-5L HRQoL at 4 months post injury. Secondary outcomes will include complications, postoperative delirium, residential status, mobility, allogenic blood use, mortality and resource use.

**Ethics and dissemination:**

NHS ethical approval was provided on 14 August 2019 (19/WA/0197) and the trial registered (ISRCTN15945622). After the conclusion of this trial, a manuscript will be prepared for peer-review publication. Results will be disseminated in lay form to participants and the public.

**Trial registration number:**

ISRCTN15945622.

Strengths and limitations of this studyPragmatic multicentre randomised controlled trial.Powered to detect differences in health-related quality of life.Inclusion of participants with and without cognitive impairment.Outcomes include the UK core outcome set for hip fracture.The trial will not capture late complications beyond 1 year post surgery.

## Introduction

Sixty-five thousand patients break their hip every year in England, Wales and Northern Ireland.^1^ Globally, the annual incidence was estimated as 1.26 million in 1990 and hip fractures were associated with 740 000 deaths.^2^ Almost all patients with a hip fracture require operative treatment; either internal fixation or arthroplasty in equal numbers.^1^ Despite efforts to rehabilitate these patients, outcomes following surgery are poor; 30-day mortality was 6.5% in 2016, with 1-year mortality estimated to be 30%; furthermore, patients reported a 25% reduction in health-related quality-of-life at 4 months, disability similar to that seen following a stroke.^1 3 4^

Patients admitted with a hip fracture are typically elderly, frail and have multiple medical comorbidities, including prefracture anaemia.^5–8^ As a consequence of the fracture and urgent surgery required, patients sustain acute blood loss, compounding this pre-existing anaemia.^9^ Postoperative anaemia is associated with increased disability, reduced muscle strength and reduced physical performance.^8 10^ Beyond the perioperative period, anaemia is associated with an increased risk of falls, hospitalisation and mortality.^8 11^ In this elderly and frail population perioperative allogenic (blood from a donor) blood transfusion is often required.^12^

Allogenic blood transfusions do not come without risks to patients. They cause an increased rate of local (eg, wound) and systemic (eg, pneumonia) infections in postoperative patients.^13^ This is attributable to the immunomodulatory effect of allogenic blood on the recipient.^13^ As well as causing infections allogenic blood use is independently associated with increased length of hospital stay in orthopaedic surgery.^14^ Rarer direct complications of allogenic blood use include death and major morbidity.^15^

The cost to the NHS of blood replacement products is high; the first unit of red cell concentrates costs £170 with subsequent units costing £162.^16^ At a single major trauma centre, the costs of allogenic blood transfusions for patients with a hip fracture are £62 272 per year (unpublished data). This extrapolates to a direct national cost of approximately £7.28 million. This estimate excludes the costs associated with an increased length of stay and treating infections and other complications of transfusion.

Concerns regarding patient safety and the costs of allogenic blood have driven efforts to reduce transfusion rates.^16^ Intraoperative cell salvage is a method of collecting blood lost during surgery with an option of transfusing it back to the patient. The cell salvage device filters, washes and centrifuges blood lost during surgery, to separate the red blood cells from non-cellular matter prior to intraoperative autotransfusion. Complications as a result of cell salvage are rare.^15^

In order to reduce the use of allogenic blood, the NICE guidelines (Blood Transfusion NG24 2015) recommended the use of cell salvage and tranexamic acid where surgical blood loss is expected to be greater than 500mls.^17^

The direct intraoperative blood loss reported across studies of hip fracture surgery is variable.^18–21^ Several randomised controlled trials report a mean intraoperative blood loss greater than 500 mL in patients undergoing different types of surgery for a fractured hip.^22–25^ When intraoperative losses are added to blood lost as a direct result of the fracture, the total blood loss is estimated to be between 550 ml-1300mL.^9^

When considering whether to use cell salvage, patients with a hip fracture present a unique population. They have a high mortality, high transfusion rates and high degrees of pre-existing morbidity including anaemia. These considerations mean that there are large potential benefits of using cell salvage in this population. Using cell salvage to reduce the use of allogenic blood has the potential benefit to patients of improving their outcomes from hip fracture surgery, by reducing infections, length of stay and levels of anaemia.

It is currently routine practice to use a restrictive transfusion policy in hip fracture surgery, but the use of cell salvage has not become embedded in this patient group. We propose evaluating the clinical and cost effectiveness of cell salvage and autotransfusion in hip fracture surgery.

### Aims and objectives

The aim of this randomised controlled trial is to compare health-related quality of life (HRQoL) in participants over 60 years of age with a surgically treated hip fracture receiving intraoperative cell salvage and autotransfusion, compared with standard care.

The primary objective is:

To quantify and draw inferences on observed differences in participants’ HRQoL between the trial treatment groups at 4 months post surgery.

The secondary objectives are:

To quantify and draw inferences on the observed differences in participants’ HRQoL between the trial treatment groups at 12 months post surgery.To investigate the risk of complications within the first 12 months post surgery between the trial treatment groups.To quantify and draw inferences on observed differences in (1) the proportion of participants suffering with delirium in the immediate postoperative period, (2) residential status at 4 and 12 months post surgery, (3) mobility at 4 and 12 months post surgery, (4) allogenic blood use during the hospital admission and (5) mortality within the first 12 months post surgery between the trial treatment groups.To quantify differences in resource use, costs and comparative cost effectiveness of the trial treatment groups in the first year post surgery.

## Methods and analysis

### Study design

A multicentre, parallel group, two-arm, standard-of-care randomised controlled superiority trial assessing the clinical and cost effectiveness of intraoperative cell salvage compared with standard care in patients undergoing surgery for a hip fracture. The trial will be embedded within the World Hip Trauma Evaluation (WHITE) Cohort; a cohort that has delivered a number of embedded RCTs in hip fracture care.^26–29^ The study is conducted in two phases: an initial feasibility phase in which the acceptability of the interventions and trial processes were tested, and a definitive phase which comprises the main trial. Feasibility data will be locked, and not analysed, at completion of that phase. At the end of the definitive main trial phase, data from the two phases will be analysed together as a single dataset.

### Eligibility

Patients will have an eligibility check by the clinical team in the daily trauma meetings. Participants will be assessed against the specific inclusion and exclusion criteria as outlined below:

#### Inclusion criteria

All patients, both those with and without capacity, presenting with a fracture of the hip (AO type A1-3, B1-3 and subtrochanteric fractures) who, in the opinion of the operating surgeon, would benefit from surgery.

#### Exclusion criteria

Patients younger than 60 years of age.Patients undergoing percutaneous (cannulated) hip screw fixation.Patients for whom the treating surgeon has already elected to use cell salvage (eg, a Jehovah’s Witness).Patients who have sustained a pathological fracture.

### Consent

Patients with a hip fracture are a clinical priority for urgent operative care. All patients with a fracture of the hip are in pain and will have received opiate analgesia. It is therefore understandable that the majority of patients find the initial period of their treatment in hospital confusing and disorientating. Similarly, patients’ next of kin, carers and friends are often anxious at this time and may have difficulty in absorbing the large amounts of information that they are given about the injury and plan for treatment. In this emergency situation, the focus is on obtaining consent for surgery (where possible) and on informing the patient and any next of kin about immediate clinical care. It is often not possible for the patient, relative or carer (consultee) to review trial documentation, consider the information and communicate an informed decision about whether they would wish to participate in the study. The consent procedure for this trial will reflect that of the surgery, with the clinical team assessing capacity before taking consent for the surgical procedure, and this capacity assessment then being used to guide the proper approach to consenting to the research. An appropriate method, in line with the Mental Capacity Act 2005 and the code of Practice 2007, and approved by the National Research Ethics Committee, will be used to gain either prospective or retrospective consent form the patient or appropriate consultee by a Good Clinical Practice (GCP)-trained, appropriately delegated member of the research team.

### Postrandomisation withdrawals and exclusion

Participants/consultees may withdraw from the study at any time without prejudice. In addition, the investigator may discontinue a participant from the study at any time if the investigator considers it necessary. Throughout the study, screening logs will be kept to determine the number of patients assessed for eligibility and reasons for any exclusion.

If the participant/consultee withdraws from the study completely, data collected from the participant or recorded in the medical record up until the point of withdrawal will be included in the final analysis. Since randomisation will occur just prior to surgery, data regarding the operation received and autotransfusion blood volume (where deemed possible) will be recorded as a minimum for all participants. Participants who decline to continue to take part once they have regained capacity will be given the opportunity to discuss/inform the research team of the reasoning behind their decision not to take part.

Similarly, data from participants who die before consent to continue participating can be obtained, will be included in the final analysis. For those participants who lack capacity, and die before advice can be obtained from the participant’s relatives/next of kin, it is our intention not to contact relatives of participants to inform them of the participant’s initial inclusion in the study to avoid distressing the relatives unnecessarily.

### Randomisation and blinding

The allocation sequence will be generated by the trial statistician. The treatment allocation will be on a 1:1 basis and will be stratified by fracture type (extracapsular vs intracapsular) and by trial centre, to ensure that any clustering effects within centres are evenly distributed between the treatment groups. The allocation will be administered using secure, online randomisation via a distant computer at Oxford Clinical Trials Research Unit (OCTRU), University of Oxford, using RRAMP software. Participants will be randomised preoperatively. The research associate will inform the surgeon and the operating theatre staff of the allocation in the immediate preoperative period.

In order to negate bias in the self-reported HRQoL outcome measures participants will be blinded to treatment allocation. The operating surgeon cannot be blinded to the allocation but they will not be involved in the assessment of outcomes. Participants will be blinded until the completion of the trial when the blinding will be broken if requested by the participants.

### Treatments

#### Preoperative assessments

Diagnosis of a hip fracture will be confirmed by a plain radiograph, as per routine clinical care. Routine investigations, anaesthetic assessment, antibiotic and venous thromboembolic prophylaxis will be used as per local policy.

#### Anaesthetic technique

A regional or general anaesthesia technique will be used for every participant as per routine clinical care. Intraoperative analgesia may be achieved by combining a local anaesthetic nerve block, paracetamol and opiate analgesia as clinically indicated.

#### Trial treatments

All participants will receive perioperative prophylactic antibiotics in accordance with current protocols agreed at each centre. Appropriate preparation, positioning and fracture reduction will be left to the discretion of the operating surgeon, as per their normal clinical practice. The need for allogenic blood products will be determined on an individual patient basis, following each centre’s blood transfusion policy. This will typically involve restrictive transfusion thresholds where asymptomatic patients with a haemoglobin concentration of less than 70 g/L are offered allogenic blood. This threshold may be higher, typically a haemoglobin concentration of less than 80 g/L in those with symptomatic anaemia or coexisting cardiorespiratory disease.

Participants will be randomly allocated to one of the treatment arms:

### Group 1: standard care

A standard suction system removes blood lost in the operating field and it is disposed of in clinical waste.

### Group 2: intraoperative cell salvage and autotransfusion

Intraoperative cell salvage aspirates blood and lavage fluids from the operative field during surgery and returns it to the cell saver device where it is filtered and stored in an Anticoagulant Citrate Dextrose Solution. The recovered fluid will be washed with saline and centrifugated. In all cases where technically sufficient blood is available for transfusion, it will be transferred into a blood-giving bag, where the washed red blood cells, suspended in saline, will be transfused intraoperatively. The volume of blood that was transfused, when this was possible, will be recorded. It will be the responsibility of the treating clinician to ensure that these data are recorded in the clinical notes at the end of surgery. Other relevant information about the operation will be collected.

#### Postoperative rehabilitation

Postoperative analgesia will be prescribed intraoperatively and reviewed by the responsible clinical teams as appropriate. In the postoperative period, as per standard of care, all participants will undergo an initial physiotherapy and occupational therapy trauma assessment. As part of standard care, an initial treatment plan with objectives will be made, recorded and commenced. The aim of this plan will be for participants to mobilise through early, active, full weight bearing.

Participants will be discharged from the acute Orthopaedic Trauma Ward at the earliest safe opportunity to the most appropriate discharge destination as determined by the multidisciplinary clinical team.

### Outcomes

Personal data collected during the study will be handled and stored in accordance with the 2018 Data Protection Act, which requires data to be anonymised as soon as it is practical to do so. The data collected from participants will be entered in linked-anonymised form to the trial database. All electronic patient-identifiable information will be stored on a secure, password-protected database at the University of Oxford, accessible only to the research team.

### Primary outcome measure

The UK Core Outcome Set for hip fracture recommends that patient benefit is best determined by a measure of health-related quality of life.^30 31^ The study primary outcome measure is EuroQol 5 Dimensions 5 Levels (EQ-5D-5L) score at 4 months post injury. EQ-5D-5L is a validated instrument comprising a visual analogue scale (VAS) measuring self-rated health and a health status instrument, consisting of a five-level response (no problems, some problems, moderate problems, severe problems and unable) for five domains related to daily activities^32 33^; (1) mobility, (2) self-care, (3) usual activities, (4) pain and discomfort and (5) anxiety and depression. Responses to the health status classification system will be converted into an overall score using a published utility algorithm for the UK population.^34^ A respondent’s EQ-VAS gives self-rated health on a scale where the endpoints are labelled ‘best imaginable health state’ (100) and ‘worst imaginable health state’ (0). It has been shown to be responsive to change,^31 35^ including when reported by proxy for those with cognitive impairment.^36 37^ Parsons *et al*^38^ modelled patient EQ-5D recovery trajectories after hip fracture surgery to assess the extent of any bias in 4 months outcomes by comparing complete case analysis, model-based projections and data imputation. They showed that imputing a utility of zero for death was a very close approximation to the much more complex projection methods, which was highly dependent on early (pre 4 months) EQ-5D score data that would not be available in the setting of a trial.^38^

### Secondary outcome measures

### Complications

All complications related to the index fracture and its treatment will be recorded. Complications will be classified as:

related systemic complications^34^ (including venous thromboembolic phenomena, death, pneumonia, urinary tract infection, blood transfusion, acute cerebrovascular incident, acute cardiac event, acute kidney injury, other).related local complications (superficial/deep infection, non/mal union, failure/removal/revision of metalwork including further surgery for intraoperative/postoperative periprosthetic fracture, injury to adjacent structures such as nerves/tendons/blood vessels, other).unrelated to the trial protocol.

The number and type of related serious adverse events up to 12 months will be recorded.

### Delirium

In line with data collection in the UK NHFD we will collect an immediate preoperative abbreviated mental test score and a postoperative (up to 3 days) 4AT score.

### Residential status

Changes in residential status provide a marker for a participant’s independence through their hip fracture recovery and is one of the recommended core outcomes for trials assessing interventions in hip fractures.^30^ It will be reported by participants or their proxy using an ordinal scale as per the NHFD: (1) own home/sheltered housing, (2) residential care, (3) nursing care, (4) rehabilitation unit—hospital bed in the current trust, (5) rehabilitation unit—hospital bed in another trust, (6) rehabilitation unit—NHS funded care home bed, and (7) acute hospital.

### Mobility

The ability to walk indoors and outdoors is rated very highly by patients.^30^ Mobility will be reported by participants or their proxy using an ordinal scale as per the NHFD: (1) freely mobile without aids, (2) mobile outdoors with one aid, (3) mobile outdoors with two aids or a frame, (4) some indoor mobility but never goes outside without help, and (5) no functional mobility using the lower limbs.

### Units of allogenic blood transfused

The use of allogenic blood products during the index hospital stay will be collected from the trial centres’ blood bank database. For each participant, the number of units transfused and the date of transfusion will be collected.

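### The donor-blood outcome spans the whole admission, so it counts units given before randomisation: precision is lost for mean units, and ratio or any-transfusion effects are also attenuated

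*Protocol article*

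**What the plan says.** The window for donor blood appears twice in the protocol article, both times as the whole stay. The secondary objectives under Aims and objectives name "allogenic blood use during the hospital admission". The section Units of allogenic blood transfused says: "The use of allogenic blood products during the index hospital stay will be collected", with the centres' blood bank records as the source. It adds: "For each participant, the number of units transfused and the date of transfusion will be collected". A date is listed; a time of day is not.

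Randomisation falls later than admission. Randomisation and blinding states: "Participants will be randomised preoperatively". Postrandomisation withdrawals and exclusion is more specific: "Since randomisation will occur just prior to surgery". The intervention acts later still. Under Group 2, "the washed red blood cells, suspended in saline, will be transfused intraoperatively".

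Statistical analysis assigns mixed-effect logistic regression to binary secondary outcomes and mixed-effect linear regression to continuous ones. It does not say which dated units enter the blood analysis, and it refers detail to a separate SAP, which is not at hand.

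**The concern.** An outcome for a randomised comparison should start no earlier than randomisation. Here it starts at admission, so it can contain events that happened before allocation existed.

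Such events are plausible on the article's own account. The Introduction describes anaemia that predates the fracture and blood lost through the fracture itself. The Trial treatments section ties donor blood to individual need under local policy, with no restriction to the period after surgery.

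The window is also out of step with the other objectives. Quality of life, complications, residential status, mobility and mortality are all timed from surgery, and delirium is placed after it. Among the clinical outcomes, only blood use is tied to admission. Blood transfusion also appears in the list of systemic complications, which the objectives count from surgery, so one kind of event has two start points.

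At stake is the outcome closest to the stated rationale for cell salvage, which is to reduce the use of donor blood.

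**Working it through.** **The plan's own figure.** No figure is given for the blood outcome. The sample size rests on EQ-5D-5L (SD 0.3, difference 0.075, two-sided 5%). The normal approximation gives 504 (80% power) and 674 (90%), against 506 and 676 stated. With a t-test, power is 80.1% at 253 per arm and 90.1% at 338 per arm, so the stated figures hold. Dividing by 0.6 gives 506/0.6 = 843.3 and 676/0.6 = 1126.7, consistent with 844 and 1128. Nothing below changes them.

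**Any transfusion, first set of assumptions.** All inputs are assumed: transfusion after randomisation in 30% of controls and 22% of the cell salvage arm; a share *p* transfused before randomisation, equal in both arms; the two events independent.

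Whole-stay risk = 1 − (1 − *p*)(1 − post-randomisation risk).

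At *p* = 5%: control 1 − 0.95 × 0.70 = 0.335; treated 1 − 0.95 × 0.78 = 0.259; risk ratio 0.259/0.335 = 0.77; odds ratio (0.259/0.741)/(0.335/0.665) = 0.69.

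| *p* | Control | Treated | Risk ratio | Odds ratio |
|---|---|---|---|---|
| 0% | 0.300 | 0.220 | 0.73 | 0.66 |
| 3% | 0.321 | 0.243 | 0.76 | 0.68 |
| 5% | 0.335 | 0.259 | 0.77 | 0.69 |
| 10% | 0.370 | 0.298 | 0.81 | 0.72 |

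**Any transfusion, second set of assumptions.** The Abstract's figure of about 30% transfused is perioperative, and the first set places extra transfusion on top of it. As a check, hold the control whole-stay risk at 30% and assume a post-randomisation risk ratio of 0.75, independence and 1128/2 = 564 per arm. The control post-randomisation risk is then 1 − 0.70/(1 − *p*). Power is the normal approximation for two proportions at two-sided 5%.

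| *p* | Whole-stay risk ratio | Power, whole stay | Power, post-randomisation only |
|---|---|---|---|
| 0% | 0.75 | 82% | 82% |
| 2% | 0.77 | 76% | 79% |
| 5% | 0.79 | 66% | 75% |
| 10% | 0.83 | 47% | 66% |

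The direction is the same. Part of the fall in power comes from fewer post-randomisation events as *p* rises. The cost of the window is the gap between the last two columns.

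**Mean units.** Assumed: post-randomisation means of 0.5 (control) and 0.375 (treated), SD 1.0, and 2 units per pre-randomisation recipient. Both arm means rise by 2*p*, so the expected absolute difference stays at 0.125. The SD becomes √(1 + 4*p*(1 − *p*)): 1.04, 1.09 and 1.17 at 2%, 5% and 10%. Power with 564 per arm falls from 56% to 52%, 49% and 44%. The ratio of means, (0.375 + 2*p*)/(0.5 + 2*p*), moves from 0.75 to 0.77, 0.79 and 0.82.

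**The case against.** The strongest reply is that the outcome section describes what is collected, not what is analysed. Because "the number of units transfused and the date of transfusion will be collected", units given on days before randomisation can be removed, and the rule for doing so may well sit in the SAP. This stands in part: no passage says that pre-randomisation units are kept in the analysis, and a reader should not infer that they will be. It does not remove the point, because the objective itself names the admission as the window. An analysis starting at randomisation would narrow that objective, and a date without a time cannot sort units given on the day of surgery.

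A second reply is that the outcome is headed as a number of units, and a linear model on units suffers no bias. This stands. A reader might infer that the window dilutes the treatment effect whatever the measure. The documents do not support that. Units given before randomisation are balanced in expectation, so the absolute difference in means is unbiased. Attenuation needs a ratio measure or a binary endpoint, and the blood outcome section defines no any-transfusion endpoint; transfusion as a yes/no event appears only in the complications list.

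A reader might also infer that a chance imbalance in preoperative transfusion would bias the comparison. It would not. It is sampling variation, which the confidence interval already covers.

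Finally, every preoperative rate used here is assumed. At 3% the odds ratio moves only from 0.66 to 0.68, which is minor for a secondary outcome. Whole-stay counts also suit the costing, since resource use is collected over the initial inpatient stay.

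**Conclusion.** The point holds in limited form. As stated, the window opens before allocation and admits units that cell salvage cannot affect. The certain consequence, wherever such units exist, is lost precision. The conditional consequence, for ratio or any-transfusion measures, is a shift toward no difference: under 30% vs 22% after randomisation, odds ratio 0.66 to between 0.68 and 0.72 and risk ratio 0.73 to between 0.76 and 0.81, for 3% to 10% transfused beforehand. These figures rest on assumed rates and on independence of transfusion before and after randomisation. The article gives no split of its perioperative 30%, so the true size could be negligible or material. The primary outcome, its analysis and the sample size are untouched.

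**What to change.** Define the analysed outcome as donor units from randomisation to discharge from the index stay, classified by the transfusion dates already collected. Enter units given before randomisation as a baseline covariate. Whole-stay units can still be reported and used for costs.

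The start should be randomisation and not incision. Theatre staff learn the allocation shortly before the operation, so units given between those two moments are post-randomisation events and should not be dropped.

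The cost is a change of wording plus one practical step. For units given on the day of surgery, either record the time, which is not among the items the article lists, or state a convention where no time is available, for example counting all day-of-surgery units as post-randomisation. Such a convention lets a few earlier units through, but it applies equally to both arms and keeps every post-randomisation unit given that day.
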